**2. Physical performance and lower extremity physical function:**

This will be measured using the following physical performance measures:

(i) The 10m Walk Test (10MWT). This test measures walking speed and functional mobility and is recorded in m/s. Gait speed is calculated as total distance/time
^
44
^.

(ii) The 2minute Walk Test (2MWT). This test of self-paced walking ability and functional capacity assesses a participants’ ability to walk unassisted over a 15m distance, as fast as possible, for two minutes. Rest breaks are permitted and the distance covered is measured
^
45
^.

(iii) The Chair Stand Test (CST). This test of lower limb strength and endurance measures the total number of sit to stand repetitions a participant can perform in 30 seconds
^
46
^.

(iv) The Single Leg Stance Test (SLS). This test of balance is performed on each leg. The participant is timed standing unassisted on one leg, with eyes open and hands placed on the hips
^
47
^.

**3. Pain:** Each participant will be questioned whether they are experiencing any pain and will be questioned about its location and duration. Severity of pain will be assessed using the Numerical Rating Scale (NRS). The NRS is a unidimensional measure of pain intensity from 0–10, with 0 being zero pain and 10 the worst pain imaginable
^
48
^.

**4. Frailty**: This will be assessed in two ways; using the Clinical Frailty Scale (CFS)
^
49
^ and the SHARE-FI
^
36
^. This scale is assessed by the tester and each point on the scale is correlated with a description of frailty along with a visual chart to aid the tester in classifying frailty from 1 (very fit) to 9 (terminally ill). Higher scores indicate higher levels of frailty. The SHARE-FI is a valid tool to measure the level of frailty in individuals aged ≥50 years
^
36
^. It consists of quick questions related of the following variables; exhaustion, loss of appetite, walking difficulties and low physical activity. Answers are entered into a freely available web calculator to generate a frailty score and a frailty category of non-frail, pre-frail and frail is generated.

**5.**
**Nutritional status** will be assessed by using the Mini-nutritional assessment (MNA) score
^
50
^. The MNA assesses the risk for malnutrition. In particular, the short form of the MNA (MNA-SF)
^
51
^ is a screening tool consisting of six questions on food intake, weight loss, mobility, psychological stress, or acute disease, the presence of dementia or depression, and body mass index (BMI). The maximum score for this part is equal to 14. A score equal to or higher than 12 indicates that the subject under study has an acceptable nutritional status thus excluding malnutrition and/or malnutrition risk, meanwhile, a score ≤ 11 implicates to proceed with the complete version of the MNA (MNA-LF)
^
51
^. As this test has not been validated for this population, the terminology of two of the questions of the MNA (regarding acuity of illness and psychological stress) have been slightly modified for the purposes of this study, ie “Have you recently been sick or in hospital?” and “Have you problems with concentration or memory?”

**6. Body Mass Index (BMI).** Height and weight will be measured and the following formula will be applied to generate BMI; kg/m
^2^.

**7. Self-report:**

**Short-Form 12 (SF-12)
^
52
^.** The SF-12 is a self-report measure of health used across age, disease and treatment groups. It uses eight domains including physical and social activities, pain, mental health, emotional health, vitality and general health perceptions to measure health. The participant completes a 12 question survey which is scored by the researcher. The minimum possible score is 12 and the maximum possible score is 48. Lower scores indicate better health. To ascertain perceptions of unmet physical health needs & rehabilitation/exercise preferences, open-ended questions will be used regarding (i) concerns with current physical health, (ii) exercise history (iii) current concerns/priorities of the participant and (iv) the final questions asks “do you have someone who looks out for you?”. This information will be transcribed by the research physiotherapist and repeated back to the participant to verify accuracy. It will not be audio-recorded.

*Reliability and validity of secondary outcomes measures have been confirmed (see
*Extended data*, Supplementary Figure).

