## Aim and objectives

The overall aim of this study is to test the feasibility and pre-post intervention impact of a low threshold physical rehabilitation programme with dietary supplementation to target frailty and poor physical functioning in people who are homeless.

Objectives:

1.To evaluate recruitment, retention and adherence to the physical rehabilitation and protein supplementation programme.2.To examine baseline and pre-post intervention change in measures of physical, nutritional and frailty status, and self-reported pain.3.To ascertain perceptions of unmet physical health needs, exercise habits and how an exercise intervention should ideally be designed to meet the needs of this cohort with lived experience of homelessness and active addiction issues.

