### Analytic plan

Our study is very much feasibility focussed and not hypothesis driven so formal power calculations are not directly applicable. Prospectively, potential participants that meet the study eligibility criteria will be invited to participate. Descriptive statistics will summarise participant demographics and feasibility measures such as attendance rates. Nominal or ordinal variables will be reported as frequencies and percentages. Continuous variables will be summarised as mean and standard deviation if normally distributed and median and inter-quartile range if non-normally distributed. Results will be compared to evaluate change over time from initial to final intervention. Normally distributed data will be compared from initial to final recorded time-points using paired t-tests and non-normally distributed data via the Wilcoxin-sign rank test. As participants will be heterogeneous, data will be sub-stratified and participants will be grouped meaningfully. Free text responses from subjective questions will be reported and organised into topic areas.

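### The SF-12 is defined as one 12–48 total over physical and mental domains, so a change in this secondary score cannot be attributed to either

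*Protocol article*

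**What the plan says.** The protocol article lists the SF-12 under Secondary outcomes, item 7 (Self-report), as a general self-report health measure. On content it says: "It uses eight domains including physical and social activities, pain, mental health, emotional health, vitality and general health perceptions to measure health". On administration: "The participant completes a 12 question survey which is scored by the researcher". On the score: "The minimum possible score is 12 and the maximum possible score is 48", and "Lower scores indicate better health". That is one minimum, one maximum and one direction. Neither this section nor the Analytic plan mentions a physical or mental component, domain scores or weights.

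Under Aim and objectives, the programme is meant "to target frailty and poor physical functioning in people who are homeless". Objective 2 reads: "To examine baseline and pre-post intervention change in measures of physical, nutritional and frailty status, and self-reported pain". For change over time the Analytic plan states: "Normally distributed data will be compared from initial to final recorded time-points using paired t-tests", with a signed-rank test otherwise. It gives no sample size and says that "formal power calculations are not directly applicable".

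**The concern.** The score adds domains that the intervention aims at to domains that it does not name as targets. Objective 2 lists physical, nutritional and frailty status and pain; mental and emotional health are not in it, yet they enter the SF-12 total with the physical domains.

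Two features of the study make movement in the mental items foreseeable. The section on obtaining consent expects mood and motivation to fluctuate, and the Discussion confirms that there is no comparator group. If the total improves, a reader may take it as a physical benefit when mood has moved. If it does not, a physical gain may have been offset by a worse mental state. The total alone does not distinguish these cases. This matters for a study whose Discussion hopes to inform a definitive trial, because the choice of a self-reported outcome depends on knowing which part of health changed.

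**Working it through.** **1. Does the stated range describe a single sum?** Inputs from item 7: 12 questions, minimum 12, maximum 48.

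- 12 / 12 = 1, so the minimum fits 12 items each with a lowest code of 1.
- 48 / 12 = 4, so the maximum fits an average top code of 4 per item.

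The range is consistent with one sum over all 12 items. The number of response levels per item is not given, so the 48 cannot be confirmed from the article.

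**2. Can a change in the total be traced to its source?** Write total change = physical change + mental change. A total change of −3 (an improvement, as lower is better) arises from each of these:

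- physical −3, mental 0
- physical 0, mental −3
- physical −6, mental +3
- physical −1.5, mental −1.5

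The total is the same in all four, so it does not identify the source. This needs no assumption beyond the sum itself.

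**3. How much would a physical-only gain shrink?** The article supplies no inputs, so these are assumptions: a physical and a mental half, equal SDs of change, correlation r between the two changes, a standardised gain dP in the physical half and dM in the mental half. Then

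standardised change in the total = (dP + dM) / √(2 + 2r).

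With dP = 0.5 and dM = 0:

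- r = 0: 0.5 / √2.0 = 0.35 (71% of the physical effect)
- r = 0.2: 0.5 / √2.4 = 0.32 (65%)
- r = 0.6: 0.5 / √3.2 = 0.28 (56%)
- r = 0.7: 0.5 / √3.4 = 0.27 (54%)

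**4. Does dilution always occur?** No. The total shows the full 0.5 when dM = 0.5 × (√(2 + 2r) − 1):

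- r = 0.2: 0.5 × 0.549 = 0.27
- r = 0.6: 0.5 × 0.789 = 0.39

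If mental health improves by 0.5 SD as well, the total shows 1.0 / √(2 + 2r) = 0.65 (r = 0.2) to 0.56 (r = 0.6), which is more than the physical effect alone. The total can thus understate or overstate the physical change, depending on what the mental items do. Step 2 holds either way.

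**The case against.** The strongest reply is that the SF-12 is not asked to measure physical function. It is presented as a general health measure under its own heading, and the abstract's list of secondary outcomes does not name it. Objective 2 is served by dedicated measures: grip strength, calf and arm girth, two walk tests, chair stand, single leg stance, a pain rating, two frailty scales and the Mini-nutritional assessment. That stands. A reader might infer that the study cannot tell physical change from mood; the documents do not support this, because only one score is affected.

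A second reply is that the size of any dilution comes from the reviewer. That also stands. The study disclaims power calculations and states no sample size, so a figure for lost power would describe a test it was never sized for. The Introduction itself notes that exercise can reduce withdrawal and anxiety symptoms in drug users, so zero mental change is not the obvious scenario.

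A third reply is that an article condenses its source, and component scoring or item coding may be set out elsewhere. This stands only in part. The article does not rule out component scores, and it does not say that items are summed without recoding; a common direction is implied by the statement that lower is better. But it does more than leave scoring open: it defines a score, and the only one it defines is the mixed total.

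Finally, the 12 answers remain available, so it would be wrong to infer that information is lost for good or that the questionnaire is of no use to a later trial. What is unsuitable is the total as the sole reported result.

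**Conclusion.** The point holds in a limited form. As defined, a pre-post change in the SF-12 total cannot be attributed to physical or to mental health. That follows from the article's own description of the domains and the range, if the range is read as a sum, which the arithmetic supports.

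Dilution of a physical-only gain is real but conditional. Under the equal-halves model the total shows 54% to 71% of the physical effect for correlations from 0.7 down to 0, and a modest mental gain removes the shortfall. These figures are illustrations, not estimates for this study.

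The consequence is confined to one secondary questionnaire in a feasibility study. The primary outcomes of recruitment, retention and adherence are untouched, and the dedicated measures of physical function, frailty, nutrition and pain keep their meaning. This is a cheap improvement, not a flaw that threatens the study's conclusions.

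**What to change.** State in item 7 and in the Analytic plan that a physical and a mental summary score will be derived from the same 12 answers and reported separately. Name the SF-12 version, the scoring method and the direction of each summary. Read the physical summary alongside the Objective 2 measures. If the 12–48 total is kept, present it as supplementary and state that all items are coded in one direction before summing.

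The cost is a few sentences and, for answers already collected, a re-scoring. No new data and no extra burden on participants are needed. The small downside is two scores to report instead of one. Separate scores would show which part of health moved; without a comparator group they would still not show that the programme caused it.

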## Data collection and management

Data will be collected pre- and post-intervention for those who complete the programme, by the research physiotherapist.

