### Obtaining consent

All potential participants will be provided with a PIL and an exercise information leaflet detailing the purpose of the data collection, the exercise intervention, potential risks and benefits and data protection rights. Due to the expected high levels of functional illiteracy, the research physiotherapist will read the study related information where applicable and will be available to answer any study related queries. Where possible there will be a seven-day gap between receipt of the PIL and obtaining consent to allow potential participations time to consider participation. Due to the anticipated fluctuation in interest levels however, and other competing priorities related to mood, motivation and active addiction issues, flexibility has been built into the consent process. This means that clients who express an interest in the programme and willingness to participate the same day as first receiving the study information can be consented and commence the programme at a time suited to them. This method was successfully employed previously in a cross-sectional study conducted with patients experiencing homelessness in St. James’s Hospital
^
6
^.

Once the research physiotherapist is satisfied that the potential participant has read (or has been read to) and fully understands the PIL, they will proceed to obtain written informed consent. Obtaining consent will take place at the first interaction with the participant prior to commencement of testing. The written consent informs participants that they are permitted to withdraw from the study at any time. Participants are given their own copy of this consent form and PIL, signed by themselves and the research physiotherapist. The research physiotherapist will be accompanied by a second research assistant.

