### Intervention

The intervention will consist of three exercise opportunities, including a twice weekly, 12-week exercise programme with nutritional supplementation. The intervention will be fully supervised and delivered by two research physiotherapists. Group exercise classes or one-to one sessions will be delivered depending on participant preference. Participants will be advised of a schedule of class times, including gender specific classes and will be allocated to a specific class based on their preference. An alternate class will be offered if participants cannot attend at their scheduled time. A ‘Park Walk’ will also be scheduled one day per week. This will be a 30-minute self-paced walk of low intensity led by the research assistant involved in this programme. This is to build up exercise frequency during the week and is building in a habit which it is hoped can be continued by participants beyond the life cycle of the project. Flexibility in programme commencement and completion dates will be provided to enable the 12-week intervention to be completed within a 15-week period of time.

The PAR-Q
^
32
^, a pre-screening questionnaire, will be conducted with participants prior to commencement of the exercise classes. The research physiotherapist will, with permission, write to the participants General Practitioner (GP) to advise them of their intention to take part in the programme and to clarify that it is safe for them to proceed with the exercise intervention. If the individual does not have a GP, the research physiotherapist will discuss this individual case with a specialist consultant in Inclusion Health based in St. James’s Hospital, Dublin. The case will be outlined in broad terms, without revealing any personal details of the participant, solely as a sounding board as to whether it would be suitable for the participant to attend or not.

The exercise intervention will focus on general fitness and will include resistance, aerobic and functional exercises, with in-built flexibility based on individual participants’ needs. The exercise component will be based on ‘core’ exercises (
Table 1) which will be adjusted to increase or decrease difficulty based on the results of the initial assessment and ability of participants, as judged by the research physiotherapist. Each session, of approximately 20 minutes duration, will commence with a warm-up and stretch of the major muscles and will end with cool-down and stretch.

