### Recruitment and retention

The numbers recruited and frequency of attendances will be recorded. Participants will be encouraged to attend all sessions if possible. Drop out will also be recorded.

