## Discussion

This protocol describes a novel and pragmatic, low threshold intervention which aims to address the known poor physical health condition of people experiencing homelessness and problematic substance use. Given this is such a novel area there is no comparator group. This study will nevertheless increase knowledge, understanding and awareness of the physical health needs of this population and facilitate a better understanding of unmet need, thus assisting in shaping future physical rehabilitation services to suit these complex and transient needs. It is hoped that this study will provide preliminary data to optimise the intervention and inform the design of a definitive randomised controlled trial, where applicable. An immediate impact may be an improvement in physical health of participants, which can be a conduit for the emergence of other positive behaviours and recovery. Overall, this research will address an intractable global societal challenge, have wide impact and improve the quality of life, health and well-being of some of our most vulnerable citizens.

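### Post-intervention measures are planned only for people who complete the programme, so every pre-post change is a completer-only estimate with selection bias of unknown direction and size for the enrolled group

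*Protocol article*

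**What the plan says.** Objective 2 is "To examine baseline and pre-post intervention change in measures of physical, nutritional and frailty status, and self-reported pain". Neither this objective nor the overall aim is limited to people who finish.

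The section on data collection and management fixes who is measured: "Data will be collected pre- and post-intervention for those who complete the programme, by the research physiotherapist". Baseline measures must in practice be taken before anyone's completion is known, and the Intervention section uses the initial assessment to set exercise difficulty. The restriction therefore bears on the post-intervention assessment.

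The Analytic plan says "Results will be compared to evaluate change over time from initial to final intervention" and then "Normally distributed data will be compared from initial to final recorded time-points using paired t-tests", with a Wilcoxon signed-rank test for non-normal data.

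On losses, the section on recruitment and retention says "Drop out will also be recorded". No comparison of leavers with completers is described. On what completing means, the Intervention section says "Flexibility in programme commencement and completion dates will be provided to enable the 12-week intervention to be completed within a 15-week period of time". It states no minimum number of sessions.

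**The concern.** Paired tests use only people with two values. If the second value is sought only from completers, the estimated change belongs to a group selected by behaviour after enrolment. Where finishing is related to how health develops, the completer mean differs from the mean for everyone who started.

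The article gives some reason to expect irregular engagement. When explaining its flexible consent process it writes "Due to the anticipated fluctuation in interest levels however, and other competing priorities related to mood, motivation and active addiction issues". That passage concerns consent rather than dropout, but the same people are then asked to attend for 12 weeks.

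The Discussion says "Given this is such a novel area there is no comparator group", so there is no control group against which a selected change could be judged. The Abstract and Discussion also intend the results as preliminary data for a possible randomised trial. A completer-only change carried forward as the effect expected in all participants could mislead that trial's planning. Final values that were never collected cannot be recovered by a later analysis plan.

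**Working it through.** **No figure to reproduce.** The article states no sample size, retention rate, expected change or standard deviation. Everything numerical below rests on assumed inputs and shows only how far the answer can move. Changes are in SDs of the individual change, and positive means improvement.

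**Step 1: who contributes.** The section on data collection restricts the final assessment to completers. The paired tests need both values. No other assessment after baseline is described for the secondary outcomes. The analysed set is therefore the completers.

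**Step 2: exact identity.** With retention r,

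completer mean - all-enrolled mean = (1 - r) x (completer mean - non-completer mean).

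Assume a completer mean of 0.50. At r = 0.5:

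- non-completers change by 0: 0.5 x (0.50 - 0) = +0.25
- non-completers also gain 0.50: 0.5 x 0 = 0
- non-completers gain 0.70: 0.5 x (0.50 - 0.70) = -0.10

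| Retention (assumed) | Non-completers 0 | Non-completers 0.50 | Non-completers 0.70 |
|---|---|---|---|
| 30% | +0.35 | 0 | -0.14 |
| 50% | +0.25 | 0 | -0.10 |
| 70% | +0.15 | 0 | -0.06 |
| 90% | +0.05 | 0 | -0.02 |

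**Step 3: normal selection model.** Let the propensity to complete and the change be jointly normal with correlation rho, and let the fraction r with the highest propensity complete. Then

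bias = rho x phi(z) / r, where z is the (1 - r) normal quantile and phi is the standard normal density.

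At r = 0.5, z = 0 and phi(0)/0.5 = 0.798. With rho = +0.3 the bias is 0.3 x 0.798 = +0.24 SD; with rho = -0.3 it is -0.24 SD.

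| Retention (assumed) | rho = -0.3 | rho = 0 | rho = +0.3 |
|---|---|---|---|
| 30% | -0.35 | 0 | +0.35 |
| 50% | -0.24 | 0 | +0.24 |
| 70% | -0.15 | 0 | +0.15 |
| 90% | -0.06 | 0 | +0.06 |

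**Reading.** The possible bias shrinks as retention rises. Its sign depends entirely on how leaving relates to change. The article supplies neither quantity.

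**The case against.** The strongest reply is that a completer mean is a valid description of completers. It is biased only if read as an estimate for all enrolled. The study is small in ambition, uncontrolled and, by its own account, not driven by hypotheses. Recruitment, retention and adherence are primary and need no final assessment. Dropout and attendance are recorded, so the extent of loss will be visible, and a later trial is conditional. All of this stands and limits the seriousness of the point. It does not remove it, because objective 2 is not worded for completers and a count of leavers does not show how they differ.

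Four stronger readings are tempting but not supported:

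- **That the changes are inflated.** This is plausible if people leave because their health worsens. However, the article does not say how leavers change, and some may leave because they feel well or have moved on. The bias can be zero or reversed.
- **That the two sections contradict each other.** The Analytic plan's wording about final recorded time-points could mean anyone's last available value. Since no intermediate assessment of these outcomes is described, it most naturally means the post-intervention assessment. This is an ambiguity to tidy.
- **That completion is wholly undefined.** A 12-week programme within 15 weeks is stated. Only a minimum attendance is absent, and the full protocol may give one.
- **That leavers are easy to reach because they still use the day centre.** Participants are its service users at entry, but nothing says that those who drop out keep attending.

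**Conclusion.** The point holds in limited form. As written, the plan makes every pre-post change in the secondary outcomes a completer-only estimate. As an estimate for all enrolled it is at risk of selection bias, plausibly towards benefit, with direction and size unknown. At an assumed 50% completing and correlations from -0.3 to +0.3, the bias lies between -0.24 and +0.24 SD; at an assumed 90% completing, the same correlations give at most 0.06 SD either way. The completer-only restriction follows from the text, whereas the figures rest on assumed inputs. Because the primary feasibility outcomes are untouched, this is a change that should be made rather than one on which the study depends.

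**What to change.** Replace the sentence on data collection with wording such as: *Baseline data will be collected from every enrolled participant. Every enrolled participant who has not withdrawn consent will be invited to a final assessment at the end of their own 12-week programme period, within the 15-week window counted from programme start, whatever number of sessions they attended.* Counting from programme start matters because start dates are flexible.

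Then, in the Analytic plan:

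- Analyse everyone with a final assessment, and show completers as a secondary set defined by a minimum attendance fixed in advance.
- Report the number of people behind each change.
- Tabulate baseline values for those with and without a final value.
- State that the final recorded time-point is this same assessment.
- If non-completers cannot be reached, label the changes as completer-only.

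Setting missing final values to no change is not recommended. It is a single imputation that understates variability, and it is not conservative if leavers get worse.

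The cost is protocol wording and some time from existing staff to re-contact people who stop attending. The reported changes may look smaller. In return, the study learns whether outcomes can be obtained from non-attenders, which is useful feasibility information for any later trial.
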